# Comparison of intradialytic neuromuscular electrical stimulation and oral nutritional supplements in hemodialysis patients: study protocol for a multicenter, parallel-group, randomized controlled trial in Korea

**DOI:** 10.1186/s13063-021-05918-x

**Published:** 2021-12-20

**Keywords:** Hemodialysis, Neuromuscular electrical stimulation, Muscle strength, Physical function, Protein supplementation, Quality of life

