However, physical inactivity is an important clinical problem among dialysis patients [27]. The Kidney Disease Outcome Quality Initiative (K/DOQI) and European guidelines recommend that nephrologists counsel and encourage dialysis patients to increase physical activity [29, 30]. Providing exercise therapy to patients who are unable to perform conventional dynamic training due to position limitations, hemodynamic instability during dialysis, low motivation, or fatigue is a major challenge [31]. HD patients, especially elderly patients, reported low levels of physical activity, which is associated with poor physical function and frailty [32].

Intradialytic exercise (IDE) can enhance or replace physical exercise in frail and exercise-hesitant HD patients. Neuromuscular electrical stimulation (NMES) induces muscle contraction by stimulating muscles or peripheral nerves, which prevents muscle atrophy due to central or peripheral muscle paralysis. NMES has the strength of application to exercise-hesitant patients. Recently, many studies have evaluated the feasibility and efficacy of intradialytic NMES. Intradialytic NMES of the quadriceps or gluteal muscles improved muscular strength, muscle cross-sectional area, functional capacity, and quality of life [33, 34]. Intradialytic NMES improved cardiorespiratory reserves (VO_2_ peak, VO_2_ anaerobic threshold) and muscle strength [31]. It also improved physical functioning and health-related QOL [35]. In addition, intradialytic NMES altered inflammatory markers, as it increased the levels of IGF-1, reduced the levels of IL-10, and reduced DNA damage in blood [36, 37]. Therefore, intradialytic NMES can also be a good option to enhance muscle strength and physical functioning as well as exercise compliance in HD patients, especially exercise-hesitant patients.

However, there has been no research about the effect of simultaneous nutritional support and NMES in dialysis patients. Therefore, we designed a 12-week trial comparing control, protein supplementation only, intradialytic NMES only, and intradialytic NMES combined with protein supplementation. In this study, we will evaluate the differential effectiveness of nutritional support and NMES during HD on muscle power, muscle mass, physical function, and QOL.

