**Fig. 1 Fig1:**
[figure not shown]
Clinical trial design

The primary endpoint was the difference in hand grip and leg muscle strength at 12 weeks among the 4 treatment groups. Secondary endpoints included the following: muscle mass; physical performance, including the 10-m walking test and timed-up-and-go test; and questionnaires about QOL, physical activity, depression, and falls.

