### Sample size

Sample size estimation was based on detecting a mean between-group difference in leg muscle strength at the end of the study. Based on the results from an earlier study [34], the rationale mean (pooled standard deviation (SD)) for calculating the sample size was 24.82 (we chose the left leg SD, which was larger than the right leg SD of that study, to approach conservatively). Therefore, the means (SDs) of leg muscles in the NMES and control groups were 26.1 (24.82) and −8.3 (24.82), respectively.

Assuming a two-tailed hypothesis, an alpha value of 0.0083 due to the correction for type 1 error according to multiple tests, and a desired power of 80%, 13 participants are needed per group to complete the study. To allow a 25% dropout rate, we will initially recruit at least 72 participants.

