## Discussion

Sarcopenia occurs early and is more severe in CKD and ESRD patients. Reduced exercise capacity and functional decline due to sarcopenia are important because of their impact on QOL and morbidity [50]. Structural and functional declines in the cardiovascular system and skeletal muscles, which determine exercise capacity and VO_2max_, were less than 75% of the predicted values in CKD patients [31]. Approximately 71% of HD patients had a decrease in quadriceps force that was less than 2 SDs from the average of normal controls [6].

Nutritional support and exercise are the main strategies to prevent and treat sarcopenia. However, malnutrition is common in dialysis patients and many patients are exercise-hesitant.

Insufficient food contributes to PEW and an increased catabolic state, including persistent inflammation, metabolic acidosis, hormonal imbalance, and physical inactivity, leads to excessive muscle wasting [2, 51–53]. Malnutrition is considered a nontraditional cardiovascular risk factor in dialysis patients. Hypoalbuminemia is one of the most potent risk factors for mortality in HD patients [54]. Sarcopenia and low exercise capacity are predictors of morbidity and mortality and show reversed epidemiological tendencies in CKD and ESRD patients [2].

Proteolysis of muscles occurs when proteins or amino acids are required. Continuous and sufficient dietary protein intake is necessary because protein is not stored [11]. Leucine, branched-chain amino acid (BCAA), or β-hydroxy-β-methylbutyrate (HMB) is usually recommended for dietary protein intake in older people. Fast proteins, such as whey protein, may be beneficial compared to slow proteins, such as casein protein [28, 55]. In addition, animal-origin proteins can be better than plant-based proteins at accelerating protein synthesis, if we set aside the control of phosphorus and accompanying conditions in CKD and ESRD patients [28]. We expect protein supplementation including whey protein, as used in this trial, can improve muscle wasting.

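### Power is shown for only one of six pairwise contrasts, NMES versus a declining control; at 13 completers per group the combination must beat NMES alone by about the whole assumed NMES effect to reach 80% power

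*Protocol article*

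**What the plan says.** The Sample size section gives one pair of assumed means: "the means (SDs) of leg muscles in the NMES and control groups were 26.1 (24.82") for NMES and −8.3, with the same SD, for control. A negative mean can only be a change in strength, so the control arm is assumed to decline. The section continues: "Assuming a two-tailed hypothesis, an alpha value of 0.0083 due to the correction for type 1 error according to multiple tests". With 80% power this leads to 13 completers per group and, after 25% dropout, 72 recruited in four equal arms. No expected mean is given for the supplement arm or the combination arm, and no power for any other contrast.

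Elsewhere the article frames the question more widely. Under Study design: "The primary endpoint was the difference in hand grip and leg muscle strength at 12 weeks among the 4 treatment groups". The title reads "Comparison of intradialytic neuromuscular electrical stimulation and oral nutritional supplements in hemodialysis patients". The Introduction names the gap, "there has been no research about the effect of simultaneous nutritional support and NMES in dialysis patients", and the aim, "we will evaluate the differential effectiveness of nutritional support and NMES during HD on muscle power, muscle mass, physical function, and QOL". Statistical methods names two-sample t-tests (or rank sum tests) for between-group comparisons, together with analysis of covariance and repeated-measures mixed models.

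**The concern.** The one contrast with a power calculation is NMES against no treatment. The Introduction and Discussion already treat that effect as supported by earlier studies. The contrasts that address the title and the stated gap are NMES versus supplement and combination versus NMES alone. Both have an active comparator, so their true differences may well be smaller than 34.4.

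Because the alpha is divided for multiple tests and the primary endpoint spans all four groups, a reader can easily take 80% power with 13 per group as describing the whole four-arm comparison. If so, a non-significant result for the combination against NMES could be read as no added benefit when the trial had little chance of showing one. That matters for a trial whose authors hope it will provide guidelines.

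**Working it through.** **Inputs (Sample size section).** NMES +26.1; control −8.3; SD 24.82 in each group; two-sided alpha 0.0083; 13 completers per group; 25% dropout. Four arms give 4 × 3 / 2 = 6 pairwise contrasts, and 0.05 / 6 = 0.00833. The article does not state the number of tests; six is inferred from this match.

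**Reproducing the plan.** Difference = 26.1 − (−8.3) = 34.4; standardised, 34.4 / 24.82 = 1.386. With z(1 − 0.0083/2) = 2.640 and z(0.80) = 0.842:

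n = 2 × [24.82 × (2.640 + 0.842) / 34.4]² = 12.6, rounded up to 13 per group.

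13 / 0.75 = 17.3, rounded up to 18 per arm; 18 × 4 = 72. Both stated figures reproduce, so the plan appears to have used the normal formula.

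**Power for NMES versus control.** The standard error of a difference at 13 per group is 24.82 × √(2/13) = 9.735.
- Normal: Φ(34.4 / 9.735 − 2.640) = Φ(0.894) = 81%.
- Two-sample t-test (noncentral t, 24 degrees of freedom, critical value 2.877, noncentrality 3.534): 74%. The t-test needs 15 completers per group for 80%.

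**Difference needed for 80% power in any pairwise contrast at 13 per group.** This uses no assumption about the supplement or combination arms.
- Normal: (2.640 + 0.842) × 9.735 = 33.9.
- Exact t: 36.6.

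The whole assumed NMES effect is 34.4, so the combination must exceed NMES alone by about that much again. As an illustration, an added gain of half the NMES effect (17.2, an assumption) would have power of 19% (normal) or 16% (t).

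**NMES versus supplement.** The supplement arm's mean change is not in the document, so the table shows a range of assumptions (13 per group, alpha 0.0083).

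| Assumed supplement change | Difference from NMES | Power, normal | Power, t |
|---|---|---|---|
| −8.3 (no effect) | 34.4 | 81% | 74% |
| −4 | 30.1 | 67% | 59% |
| 0 (decline halted) | 26.1 | 52% | 44% |
| +5 | 21.1 | 32% | 27% |

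If all 18 per arm completed, the row with a change of 0 would give 70% (normal) or 64% (t).

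**Combination versus supplement alone.** If the two effects are additive (assumption), this difference is again 34.4 and the power is the same as for NMES versus control: 81% / 74%.

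**The case against.** The Sample size section names its contrast openly and nowhere claims 80% power for all six comparisons. Correcting alpha for multiple tests is an error allowance, not a power claim for each test. NMES versus control is itself one of the primary four-group contrasts, and since the article reports no earlier research on the combination, sizing on the contrast with data is a normal choice. All of this stands. The sizing is relevant but incomplete, and the remedy is to state its scope.

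A reader might infer that the plan's own figures give about 50% power for NMES versus supplement. They do not. The 26.1 is the NMES arm's mean; it becomes a between-arm difference only if the supplement change is assumed to be 0. The Discussion says "We expect protein supplementation including whey protein, as used in this trial, can improve muscle wasting", but that gives no size for strength and cannot fix the value at 0 or anywhere else. A reader might also infer that the combination is under-powered against both of its components. Under additivity, the contrast with supplement alone is not affected.

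The figures also depend on 13 completers and alpha 0.0083. More completers, or mixed models that use partial data, would raise power. Statistical methods sets significance at p < 0.05; at that level the 26.1 case with 13 per group has 73% by the t-test. Which alpha governs is a separate question. The calculation here follows the one used to size the trial.

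Finally, nothing in the article says that a null result will be reported as no difference, and confidence intervals are already promised. The risk is one of reading, but the fix costs little.

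**Conclusion.** The point holds in a limited form. Power is shown for one of six pairwise contrasts, while the primary endpoint covers four groups and the stated gap is the combination. At the plan's SD, alpha and 13 completers per group, 80% power requires a difference of about 34 (normal) to 37 (t). Combination versus NMES alone reaches that only if supplementation adds about as much on top of NMES as NMES is assumed to add over no treatment. The contrast that was sized has 74% power, not 80%, by the named t-test. These results use only stated inputs.

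No single power can be given for NMES versus supplement. It ranges from 81% / 74% down to 32% / 27% over assumed supplement changes from −8.3 to +5. The documents do not support calling the sizing wrong for the endpoint as a whole, or saying that every contrast involving the combination is weak.

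**What to change.** In Sample size:
- State that the power applies to NMES alone versus control on leg strength.
- Give that power by the planned t-test: about 74% at 13 completers per group.
- State that every other pairwise contrast needs a difference of about 37 for 80% power at 13 completers per group and alpha 0.0083.
- If a power for NMES versus supplement is given, label the supplement mean as an assumption and show a range.

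In Statistical methods, state that NMES versus supplement and combination versus NMES alone are interpreted through estimates with confidence intervals, and that a non-significant result will not be reported as no difference or no added benefit.

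This is a change of wording, with no extra patients or measurements. The cost is a less favourable stated power and more limited conclusions from these two contrasts.

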## Methods/design

### Study design

The study protocol was designed in accordance with the SPIRIT guidelines [38]. This is a 12-week, randomized controlled, parallel-group, multicenter trial of intradialytic NMES and protein supplementation for HD-dependent ESRD patients. Seventy-two patients receiving HD will be randomly assigned in a 1:1:1:1 ratio to the control, intradialytic NMES only, protein supplementation only, and intradialytic NMES combined with protein supplementation groups. Measurements will be scheduled for all patients at baseline and at follow-up every 4 weeks for 12 weeks; the measurements will include vital signs; blood and urine laboratory exams including total protein, albumin, total cholesterol, calcium, phosphorus, blood urea nitrogen (BUN), serum creatinine (SCr), total CO_2_, intact parathyroid hormone (PTH), highly sensitive C-reactive protein (hs-CRP), urine urea nitrogen/normalized protein catabolic rate (nPCR), and Kt/V; and body composition including bioelectric impedance study, physical performances, and questionnaires. Figure 1 presents a flowchart of the trial procedures.

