### Statistical methods

The statistical processing will be performed with PASW advanced statistics (SPSS Inc, Chicago, IL) version 20.0 and according to an intention-to-treat principle. Data will be reported as the mean, standard deviation, and confidence intervals or in percentage frequencies. The Shapiro-Wilk test will evaluate the normal distribution of the variables. Evaluation variables, including muscle strength, performance tests, and questionnaire surveys, will be analyzed at baseline and after 4, 8, and 12 weeks by using paired *t*-tests or Wilcoxon signed-rank tests. Outcomes will be compared between groups by using two-sample *t*-tests or Wilcoxon rank sum tests according to normality. Analysis of covariance will also be conducted. The between-group differences in the outcome measures after the intervention will be calculated using repeated measure mixed models with patients as random effects, and group and time as fixed effects, and adjustments for baseline imbalances. The Spearman rank test or Pearson product-moment correlation coefficient analysis may be used to analyze the associations between clinical data and outcome measures. Statistical significance is set at a *p* value < 0.05. There is no plan for any interim analysis or stopping data collection. There are no planned subgroup analyses for any of the primary or secondary outcomes.

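### The sample size uses a multiplicity-corrected alpha of 0.0083, but the analysis section sets an unqualified p < 0.05; one decision rule covering both primary strength measures is needed

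*Protocol article*

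**What the plan says.** Under Sample size, the protocol article bases the calculation on leg muscle strength. The level it uses is "an alpha value of 0.0083 due to the correction for type 1 error according to multiple tests". The test is two-sided and the target power 80%, which leads to 13 completers in each arm. Enrolment is then raised for losses: "To allow a 25% dropout rate, we will initially recruit at least 72 participants".

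Under Statistical methods, it plans two-sample t-tests or their rank-based counterparts between groups, analysis of covariance, and repeated-measures mixed models with group and time as fixed effects. One sentence then covers all of these: "Statistical significance is set at a *p* value < 0.05". The 0.0083 does not reappear there.

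The article has four arms ("Seventy-two patients receiving HD will be randomly assigned in a 1:1:1:1 ratio"). Under Study design, in the text after Fig. 1, it says: "The primary endpoint was the difference in hand grip and leg muscle strength at 12 weeks among the 4 treatment groups". The Primary outcomes section likewise names both hand grip and leg strength as primary.

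**The concern.** The article states two significance levels that can both be read as the rule for the primary between-group contrasts. The authors recognised the multiplicity of a four-arm comparison and enrolled for it, but the sentence governing the analysis does not carry the correction forward. An analyst could follow either section and claim to follow the protocol, and the choice could be made after the p-values are known. If the 0.05 sentence prevails, the type I error protection that determined the sample size is lost.

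There is a second layer. The 0.0083 accounts for six comparisons on one measure, while two measures are primary. Carrying 0.0083 into the analysis would therefore not, by itself, hold the overall error at 0.05.

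**Working it through.** **Inputs.** All are from the Sample size and Study design sections unless marked.
- Means and SDs: "NMES and control groups were 26.1 (24.82) and −8.3 (24.82), respectively", so the difference is 26.1 + 8.3 = 34.4 and the SD is 24.82.
- Two-sided alpha 0.0083, power 80%, dropout 25%, four equal arms.
- Analysis threshold 0.05 (Statistical methods).
- Within-patient correlation between hand grip and leg strength: not given. Assumed values are 0, 0.5 and 0.7.

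**Step 1. What 0.0083 stands for.** Four arms give 4 × 3 / 2 = 6 pairs, and 0.05 / 6 = 0.00833. The match is close enough to infer a Bonferroni correction for six contrasts on one measure.

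**Step 2. Reproduce the plan's figure.** n per group = 2 × [SD × (z for alpha/2 + z for power) / difference]².
- At 0.0083: 2 × [24.82 × (2.640 + 0.842) / 34.4]² = 12.62, rounded up to 13. Then 13 / 0.75 = 17.3, rounded up to 18, and 18 × 4 = 72. This agrees with the article.
- At 0.05: 2 × [24.82 × (1.960 + 0.842) / 34.4]² = 8.17, rounded up to 9. Then 9 / 0.75 = 12, and 12 × 4 = 48.

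The corrected level thus determined enrolment. The two thresholds correspond to designs of 72 and 48 patients.

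**Step 3. Familywise error for one measure, no true differences.** The six contrasts share arms and are correlated, so the relevant quantity is the range of four means. The chance that any pair exceeds the two-sided critical value z is P(studentized range of 4 > z × √2).

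| Method | Each test at 0.05 | Each test at 0.0083 |
|---|---|---|
| Studentized range, large sample | 20.3% | 4.1% |
| Pooled-variance t, 13 to 18 per arm | 19.8-20.0% | 4.0% |
| Simulated separate t-tests, 100,000 runs, 13 or 18 per arm | 20.1-20.4% | 4.0-4.2% |

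For comparison, six independent tests at 0.05 would give 1 − 0.95⁶ = 26.5%, and the Bonferroni bound is 6 × 0.05 = 30%.

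**Step 4. Both primary measures, twelve tests.** Same simulation, 13 per arm.

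| Assumed correlation | Each test at 0.05 | Each test at 0.0083 |
|---|---|---|
| 0 | 36.5% | 8.1% |
| 0.5 | 34.1% | 7.6% |
| 0.7 | 31.6% | 7.2% |

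With 18 per arm the figures are nearly the same: 36.4% to 31.5% at 0.05, and 8.2% to 7.3% at 0.0083.

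**Step 5. Cost of covering all twelve contrasts.** The first threshold becomes 0.05 / 12 = 0.0042. The formula in Step 2 then gives 14.31, rounded up to 15 per group; 15 / 0.75 = 20, and 20 × 4 = 80. With 13 completers per group, power by the same normal approximation falls from 81.4% at 0.0083 to 74.8%. By the noncentral t distribution, the corresponding figures are 73.7% and 64.3%.

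**The case against.** The strongest reply is that correction is the declared intent. The Sample size section says so, and the later 0.05 could be the overall level against which adjusted p-values are compared. On that reading the sections agree. A related reply is that the mixed model's four-level group factor allows an overall test, which suits an endpoint worded as a difference among four groups. If that test acted as a gate, error with no true differences would be about 5% per measure. It can also be said that the threshold sentence is general, covering paired tests, correlations and questionnaires, and that a condensed article may leave testing details to an analysis plan that is not shown.

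Part of this stands. A reader might infer from the 0.05 sentence that the trial will run at 20% familywise error. The article does not support that as a fact; it follows only if the sentence is applied as written to six uncorrected contrasts. Nor is it a fault that a condensed article omits a testing hierarchy.

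The conflict itself remains. Statistical methods mentions neither adjusted p-values nor a gate, and its threshold is not limited to secondary outcomes. An overall gate would also not protect the remaining comparisons once one arm truly differs. An unseen analysis plan could follow either number and be consistent with one section of the article.

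**Conclusion.** The point holds as an unreconciled threshold, and it should be settled before results are seen. The size of the problem is conditional. Applied literally with no true differences, the 0.05 sentence gives about 20% familywise error for one measure and about 31-37% across both, against about 4% for one measure at 0.0083. These figures assume all six pairwise contrasts are tested with two-sample t-tests on normal data with equal variances and equal arms. The two-measure range also rests on the assumed correlations of 0.7 down to 0. The number six is inferred from four arms and from 0.05/6.

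A reader might also infer that the sample size is wrong, or that writing 0.0083 into the analysis section would be enough. Neither follows. The stated 13 per group and 72 in total are reproduced at 0.0083 by the standard formula. But 0.0083 per test on each of two primary measures still leaves about 7-8% across the two.

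**What to change.** In Statistical methods, replace the blanket threshold with a statement that 0.05 is the familywise two-sided level for the week-12 primary between-group contrasts. Then define a family that covers both primary measures. Two options would do this:

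1. Test the six leg-strength contrasts, on the variable used for sizing, with Holm's procedure at familywise 0.05 (smallest p against 0.0083). Make hand grip a key secondary outcome, or test it only under a pre-stated gate that preserves the 0.05. Holm is never less powerful than the Bonferroni level used for sizing, so the existing calculation still applies.
2. Apply Holm to all twelve contrasts (smallest p against 0.0042). The stated 80% power at 0.0083 then no longer applies and should be restated, as in Step 5 of the working.

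Under either option, unadjusted 0.05 applies only to outcomes outside that family.

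The cost is a short amendment and a decision about the standing of hand grip. Some primary contrasts with nominal p < 0.05 could no longer be called significant. Enrolment is unchanged at 72; under the second option the reduced power is accepted and reported. The Trial status section describes the trial as still recruiting, so the change can precede the results.

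### At the sample-size alpha of 0.0083, the named two-sample t-test has 74% power at 13 per group, not 80%; Tukey contrasts from a four-arm model already planned would give about 80%, once Sample size and Statistical methods are aligned

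*Protocol article*

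**What the plan says.** Study design has patients "randomly assigned in a 1:1:1:1 ratio to the control, intradialytic NMES only, protein supplementation only" and the combination. The endpoint paragraph of the same section reads: "The primary endpoint was the difference in hand grip and leg muscle strength at 12 weeks among the 4 treatment groups".

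Sample size works from one contrast in leg strength: "the means (SDs) of leg muscles in the NMES and control groups were 26.1 (24.82) and −8.3 (24.82), respectively". The test is two-sided ("Assuming a two-tailed hypothesis"). Its level is given as "an alpha value of 0.0083 due to the correction for type 1 error according to multiple tests". For the number of completers, the section asks for "a desired power of 80%, 13 participants are needed per group to complete the study". Enrolment follows: "To allow a 25% dropout rate, we will initially recruit at least 72 participants".

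Statistical methods says: "Outcomes will be compared between groups by using two-sample" t-tests or rank sum tests, depending on normality. It adds ANCOVA, and then a repeated-measures mixed model with group and time as fixed effects and adjustment for baseline imbalance. It sets significance at p < 0.05. It does not repeat 0.0083, name a multiplicity procedure, or say which of the three between-group analyses is primary.

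**The concern.** There are two linked problems.

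- **The stated power does not belong to the named test.** With 24 degrees of freedom and a small alpha, the normal approximation behind the 13 per group is noticeably optimistic. The two-sample t-test misses 80%.
- **The two sections describe different error control.** One corrects to 0.0083; the other tests at 0.05 with no correction. At 0.0083 the separate t-tests are underpowered. At 0.05 the six pairwise comparisons carry a large familywise error.

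The choice of method also matters at this size. A separate t-test estimates the SD from its own two arms (24 df), whereas a four-arm model supplies 48 df. A Bonferroni-type correction also ignores the known correlation among the six differences, which Tukey's procedure uses.

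**Working it through.** **Inputs (all from Sample size).** Difference 26.1 − (−8.3) = 34.4; SD 24.82; two-sided alpha 0.0083; 13 completers per group; 25% dropout. The document does not explain 0.0083. I infer 0.05/6 = 0.00833, since four arms have 4 × 3 / 2 = 6 pairs.

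**Reproducing the plan's figure.** Standardised difference 34.4/24.82 = 1.386. Normal approximation: n = 2 × (2.640 + 0.842)² / 1.386² = 12.6, so 13 per group, with 81.4% power. Dropout: 13/0.75 = 17.3, so 18 per arm and 72 in total. Both stated figures reproduce.

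**Power of the named test.** Standard error 24.82 × √(2/13) = 9.735; noncentrality 34.4/9.735 = 3.534. Power comes from the noncentral t distribution. The Tukey critical value is the 95% studentized-range quantile (4 groups, 48 df) divided by √2.

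| Method at 13 per group | df | Critical t | Power |
|---|---|---|---|
| Two-sample t at 0.0083 | 24 | 2.877 | 73.7% |
| Four-arm pooled SD at 0.0083 | 48 | 2.754 | 77.8% |
| Four-arm Tukey, familywise 5% | 48 | 2.661 | 80.4% |

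The two-sample t-test at 0.0083 reaches 78.2% with 14 per group and 82.0% with 15, so 15 are needed for 80%. At the planned dropout, 18 × 0.75 = 13.5 complete per arm.

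**Splitting the gain.** Pooling the variance adds 77.8 − 73.7 = about 4.0 points before rounding. The Tukey critical value (per-pair alpha 0.0106) adds 80.4 − 77.8 = 2.6 points. At SD 24.82 the smallest significant difference falls from 2.877 × 9.735 = 28.0 to 2.661 × 9.735 = 25.9.

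**Familywise error for one endpoint at one time point.** Simulated with 200,000 runs, 13 per arm, equal means and equal variances:

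- six two-sample t-tests at 0.0083: about 4.1%;
- Tukey: about 5.0%;
- six two-sample t-tests at the 0.05 of Statistical methods: about 20% (each test then has about 92% power).

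**Sensitivity to unequal variance.** No SD is given for the two protein arms. As an assumption, I set it to 1.5 × 24.82 in one or both of them and kept 24.82 for NMES and control. Simulated results for the NMES–control contrast:

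| Protein arms at 1.5 × SD | Two-sample t, 0.0083 | Pooled, 0.0083 | Tukey | Tukey familywise error |
|---|---|---|---|---|
| None | 74% | 78% | 80% | 5% |
| One | 74% | 65% | 68% | about 5.5–5.8% |
| Both | 74% | 52% | 56% | about 5.7–5.8% |

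**The case against.** **The planned models already use all four arms.** Statistical methods lists ANCOVA and says the mixed model, with group as a fixed effect, will give the between-group differences after the intervention. Such a model would ordinarily be fitted to all four arms and pool their variance. This stands. It limits what Tukey itself adds to about 2.6 points, because the other 4.0 come from pooling. It does not settle which analysis is primary or at what level it is tested.

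**Bonferroni is valid, and the adjustment method can be left to the SAP.** Also true. The article condenses a fuller protocol and the SAP is not shown. But the alpha, the power, the test and the significance level are all stated here, and they do not fit together.

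**Separate tests are more robust.** If the protein arms vary more, pooling costs power on the NMES–control contrast and Tukey slightly exceeds 5%, as the last table shows. This stands as a limit. It rests on an assumed SD, and it applies equally to any pooled model already planned.

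**Tukey is exact only for balanced arms, common variance and no covariates.** After dropout and baseline adjustment it is approximate, and 80.4% is not the power of the adjusted model. This stands, and the power statement should say so.

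**Conclusion.** The concern holds in a limited form. At 13 per group and alpha 0.0083, the named two-sample t-test has 73.7% power, about 6 points below the stated 80%. That figure is reached only by the normal approximation (81.4%). The correction used for sizing is not carried into Statistical methods, where 0.05 would mean about 20% familywise error over six pairs. Tukey contrasts from a four-arm model reach 80.4% at about 5%, for one endpoint at one time point.

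This rests on reading 0.0083 as 0.05/6, on a common SD of 24.82 in all four arms, on 13 completers in each, and on an unadjusted model.

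Two stronger readings are tempting, and the document supports neither:

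- A reader might infer that no planned test uses all four arms, so that the whole 6.6-point gain (73.7% to 80.4%) is owed to Tukey. The ANCOVA and mixed model contradict that. Against pooled contrasts at 0.0083 the gain is about 2.6 points.
- A reader might infer that the plan firmly controls all six pairs with Bonferroni-corrected two-sample tests. The 0.0083 appears only under Sample size, and nothing says the tests will be run at that level.

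Nor would Tukey keep 5% for the trial as a whole. It covers one endpoint, and hand grip and leg strength are both primary.

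**What to change.** - **Statistical methods:** name one four-arm model already planned (the ANCOVA, or the week-12 contrasts of the mixed model) as the primary between-group analysis. Report the six differences with Tukey-adjusted p values and simultaneous 95% confidence intervals at familywise 5% per endpoint.
- **Sample size:** align it with that analysis. State power at 13 per group as about 80% for Tukey contrasts in an unadjusted four-arm model with common SD 24.82. For comparison, give 78% for pooled contrasts at 0.0083 and 74% for separate two-sample t-tests.
- **Assumptions:** state that equal variance is assumed in all four arms and that the adjustment is approximate with unequal completers or covariates.
- **Separately:** say how hand grip and leg strength share the 5%.

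The cost is wording, settled before analysis; the adjustment is standard software output and no extra patients are needed. The downside is reliance on equal variance: if the protein arms vary more than the other two, the power gain on NMES versus control can reverse.
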